#### Uncertainty and sensitivity analysis

We will incorporate deterministic sensitivity analysis to explore multiple scenarios. Scenario analysis will be undertaken to assess the impact on the costs for different cost components including health services and the criminal justice system. For example, assuming the percentages of alcohol-related ambulance call-outs required hospitalisation if we do not get a reliable estimate from the published literature (different cost scenarios could include the associated costs, if 5%, 10% or 15% of the conveyed alcohol-related ambulance call-outs required hospitalisation). Similarly, we will create cost scenarios for recorded crimes by assuming percentages of recorded crimes incurred anticipation costs (eg, cost of burglar alarm, CCTV) or consequence costs (eg, cost of stolen property or damage) or in response costs (eg, cost of police and justice system). Moreover, we will also integrate findings from two qualitative studies within the ELEPHANT study and will adapt retailer and third-sector organisations’ perspective in the sensitivity analysis.

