Social service sector (third sector) costs include expenses incurred by voluntary organisations engaged in the NTE, such as volunteer training, medical kits and paramedic services. Consumers’ additional costs during the expanded hours include costs on alcohol, food and other items. Findings from qualitative studies and secondary sources, such as the websites of voluntary organisations, will be used to identify, measure and value the costs to the social service sectors. However, due to a lack of available data, we will not be able to measure the additional costs to consumers during the later trading hours.

Different cost components from multiple sectors are also associated with the primary (alcohol-related ambulance call-outs) and secondary outcomes (all ambulance call-outs and reported crimes). Alcohol-related ambulance call-outs are associated with the costs of major alcohol-related healthcare services including alcohol-related hospital admission, alcohol-related emergency services and ambulance service cost. Costs associated with reported crimes relate to three main cost areas: costs in anticipation of crime, costs as a consequence of crime and costs in response to crime.^64^ The costs of ambulance services and alcohol-related healthcare services will be measured using existing national Information Services Division (ISD) Scottish Health Service cost data. The ISD data will provide the unit cost of each alcohol-related ambulance service, as well as the cost of any subsequent health service utilisation. We will collect ambulance call-out data and whether these call-outs conveyed to hospital or not. If conveyed to the hospital, this will incur costs for the A&E department along with the cost of ambulance services. If an ambulance call does not convey to hospital, this will incur only the cost of ambulance services. Further, we will explore existing evidence from the literature on the percentage of alcohol-related ambulance call-outs that necessitate hospitalisation. Otherwise, we will analyse the costs within the A&E department only due to lack of data to link ambulance call-outs with hospitalisation and will incorporate them into the scenarios analysis. The unit cost for the reported crimes will be adopted from published sources, for example, ‘the economic and social costs of crime’.^64^

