### Economic data analysis

#### Analysis of costs and consequences

The economic evaluation will be conducted separately for Glasgow and Aberdeen. First, we will evaluate the impact of policy changes on harms, then we will conduct a CEA, cost analysis and CCA. Regression methods will be used to estimate effectiveness, that is, the impact of policy changes in Aberdeen and Glasgow. We will fit autoregressive integrated moving average (ARIMA) models with the weekly total counts for the primary and secondary consequences to assess the impact of policy changes (table 1). Such models account for autocorrelation and underlying temporal trends, and we will use Akaike information criterion and Bayesian information criterion to determine the best fitting ARIMA models. After a best fitting model is determined, we will then add the intervention variables to measure the effect size (impact of policy changes).

We will assess whether changes in the primary outcome (alcohol-related ambulance call-outs) have been caused by later trading hours. Where fewer or greater numbers of alcohol-related ambulance call-outs are found to have resulted from the policy changes, the unit cost of each resource will be multiplied by the absolute number of fewer or additional outcomes/consequences, for each city, before and after the policy changes.

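### No stated step carries the sampling uncertainty of the estimated policy effect into the cost results

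*Protocol article*

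**What the plan says.** Under Analysis of costs and consequences, the protocol article fits ARIMA models to weekly total counts of the primary and secondary outcomes, separately for Glasgow and Aberdeen. It then adds intervention terms to estimate the effect. The costing rule opens with a condition: "Where fewer or greater numbers of alcohol-related ambulance call-outs are found to have resulted from the policy changes". Once that condition is met, the cost is a simple product: "the unit cost of each resource will be multiplied by the absolute number of fewer or additional outcomes/consequences". The Subgroup analysis section applies the same sequence, from estimated extra or fewer call-outs to a total cost, by sex, age group and deprivation.

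The section Uncertainty and sensitivity analysis names one method: "We will incorporate deterministic sensitivity analysis to explore multiple scenarios". It goes on: "Scenario analysis will be undertaken to assess the impact on the costs for different cost components including health services and the criminal justice system". The examples are:
- costs "if 5%, 10% or 15% of the conveyed alcohol-related ambulance call-outs required hospitalisation", to be used if no reliable published percentage is found;
- for crime, "we will create cost scenarios for recorded crimes by assuming percentages of recorded crimes incurred anticipation costs", or consequence or response costs, with no percentages given;
- the retailer and third-sector perspectives.

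None of these varies the estimated effect. The Study design section says that the interrupted time series permits statistical inference, and the Reporting section names economic reporting guidelines. Neither says that the effect's uncertainty will be carried into costs.

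**The concern.** Incremental cost is a product of two factors. The number of extra or fewer events is an estimate with a standard error; the unit cost comes from published sources. The plan varies how events are costed and leaves the estimated number fixed. A range of costs built this way is not a statement of how well the cost is known.

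If the effect's 95% confidence interval includes zero, the data are compatible with no extra cost or with a saving for that outcome. Scenarios that multiply one positive number by different unit costs will all be positive. Licensing boards, whom the article names as users of the results, could be shown a strictly positive cost range that the evidence does not support. Subgroup costs are more exposed still, because they rest on smaller counts.

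**Working it through.** The document states no effect size, standard error, power, unit cost or cost result, so there is no figure to reproduce. The check asks how far each source of uncertainty can move the cost on the plan's own formula.

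**1. Effect uncertainty.** Let z = estimated effect / its standard error. With cost = unit cost × effect and the unit cost fixed, the 95% interval for cost, as a multiple of the point cost, is 1 ± 1.96/z. The values of z are assumed.

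| z | 95% interval, multiple of point cost |
|---|---|
| 1 | −0.96 to 2.96 |
| 1.96 | 0.00 to 2.00 |
| 2.8 | 0.30 to 1.70 |
| 3.92 | 0.50 to 1.50 |
| 5 | 0.61 to 1.39 |

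Below z = 1.96 the interval contains both a cost and a saving.

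**2. Hospitalisation scenarios.** Let A be the ambulance cost, c the share conveyed, E the A&E cost, I the inpatient cost and h the share of conveyed call-outs admitted. Cost per call-out = A + c(E + hI). With r = cI/(A + cE), this is proportional to 1 + hr. Moving h from 10% to 5% or 15% changes the cost by ± 0.05r/(1 + 0.10r):
- r = 1: 0.05/1.10 = ±4.5%
- r = 5: 0.25/1.50 = ±16.7%
- r = 10: 0.50/2.00 = ±25%
- r very large: approaches ±50% and never reaches it

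**3. Comparison.** The effect's interval is wider than the scenario range when 1.96/z exceeds the scenario half-width.
- Any unit costs: z below 1.96/0.50 = 3.92.
- r = 10: z below 1.96/0.25 = 7.84.
- r = 5: z below 1.96/0.167 = 11.76.

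The Consequences section also allows for costing A&E only (h = 0). Against the 10% case that lowers cost by 0.10r/(1 + 0.10r), which is always less than 100%. The sign still cannot change.

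**4. Is a small z plausible?** The effect is estimated at city level, with 10 of 1350 outlets exposed in Glasgow (0.7%) and 38 of 430 in Aberdeen (8.8%). As an illustration only, assume a simple step change, 30 to 100 events a week, overdispersion 2, AR(1) correlation 0.3, and 223 weeks before and 49 after. Those week counts suit Glasgow with the series cut at the pandemic closures; they do not describe Aberdeen.

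SE per week = √(m/223 + m/49) × √(2 × 1.3/0.7)
- m = 100: SE 3.04; half-width 1.96 × 3.04 = 6.0 events, 6.0% of baseline, about 310 a year.
- m = 30: SE 1.67; half-width 3.3 events, 10.9% of baseline, about 170 a year.

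For an assumed effect of +5% of baseline, those half-widths are about ±120% and ±220% of the point cost.

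**5. Crime costs.** The plan gives neither the scenario percentages nor the unit costs, so the comparison in step 3 cannot be made.

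**The case against.** The article is a condensed document. It does not say that deterministic analysis is the only kind planned, and its scenarios are introduced as examples. A separate statistical analysis plan exists and may report the effect's interval. That tempers the wording: the fair statement is that no stated step carries the uncertainty into costs. It does not remove the point. Costing and its uncertainty are this article's own subject, the costing rule is explicit, and the uncertainty section names its method and what it varies. An interval for the effect reported elsewhere would still not be an interval for cost.

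Three stronger readings are tempting and not supported:
- **Only significant effects will be costed, and others set to zero.** The conditional wording "Where fewer or greater numbers of alcohol-related ambulance call-outs are found to have resulted from the policy changes" allows this reading, but it states no p-value or significance rule, it covers both directions, and it follows a sentence about causation. It is ambiguous, no more.
- **Extra events are assumed to have the average case mix.** The Consequences section costs conveyed and non-conveyed call-outs differently, and the crime data record offence type. On crime the article says "The unit cost for the reported crimes will be adopted from published sources", with no statement that one average cost applies to all offences. How the mix of the extra events is obtained is unstated, not fixed wrongly.
- **Effect uncertainty dominates every cost result.** This is shown only against the hospitalisation scenarios, and only for z below 3.92 when the unit costs are unknown.

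**Conclusion.** The point holds in this form. Followed as written, the plan produces outcome costs whose ranges omit the sampling error of the policy effect, in all the economic analyses and in the subgroup costs. The cost-component scenarios cannot change the sign of an outcome's cost, so they cannot show compatibility with zero or a saving. This follows from the formula and needs no assumed inputs.

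On size, the omitted uncertainty exceeds the 5/10/15% hospitalisation scenarios whenever z is below 3.92, for any unit costs. An effect exactly at the two-sided 5% threshold gives ±100% of the point cost, against less than ±50% from those scenarios. The ±120% to ±220% figure is a Glasgow illustration on assumed inputs and should not be quoted as a property of the trial. The point estimate of cost is not biased by this gap; what is misstated is its precision.

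**What to change.** In Uncertainty and sensitivity analysis, add that for each city and outcome, and for each subgroup that is costed, the estimated effect is costed whatever its p-value. Report a 95% interval obtained by carrying the effect's confidence limits, or draws from its estimated distribution, through the costing. Keep the deterministic scenarios alongside.

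In Analysis of costs and consequences, reword the condition "Where fewer or greater numbers of alcohol-related ambulance call-outs are found to have resulted from the policy changes" so that it cannot be read as costing only significant effects.

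Multiplying the confidence limits by the unit cost closes the gap. Joint simulation of unit costs or a separate model of weekly cost would be optional additions and would need further assumed inputs. The change uses models already planned and no new data. Its cost is a little more analysis work and wider reported cost ranges.

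### Incremental costs are planned as unit cost times a point estimate, with deterministic scenarios only, so the sampling error of the policy effect is not carried into them

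*Protocol article*

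**What the plan says.** Under Analysis of costs and consequences, the effect is a regression estimate: "We will fit autoregressive integrated moving average (ARIMA) models with the weekly total counts for the primary and secondary consequences". Intervention terms are then added to the best-fitting model to give the effect size. Cost follows as a product: where more or fewer call-outs are found to result from the policy, "the unit cost of each resource will be multiplied by the absolute number of fewer or additional outcomes/consequences", separately for each city.

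Under Uncertainty and sensitivity analysis, the method is "We will incorporate deterministic sensitivity analysis to explore multiple scenarios". Three elements are described:

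- **Hospitalised share.** An example applies "if we do not get a reliable estimate from the published literature", with costs shown "if 5%, 10% or 15% of the conveyed alcohol-related ambulance call-outs required hospitalisation".
- **Crime costs.** "we will create cost scenarios for recorded crimes by assuming percentages of recorded crimes incurred anticipation costs", or consequence or response costs. The percentages are not given.
- **Perspectives.** "we will also integrate findings from two qualitative studies within the ELEPHANT study", to bring in retailers and third-sector organisations.

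Subgroup analysis repeats the estimate-then-cost sequence by sex, age group and deprivation quintile. Study design remarks that an interrupted time series permits statistical inference, and it cites a separate statistical analysis plan in connection with control selection.

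**The concern.** Each effect-derived cost has two uncertain factors: the number of events attributed to the policy and the cost per event. The described sensitivity analysis varies the second factor, or adds further cost lines. The first factor has a standard error, but no step carries it into a cost.

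A reader of the cost tables would see a range that treats the effect as known. This matters because the article says the results will go to licensing boards before publication. It matters most where the effect is small or counts are low. The effect is estimated at city level although few premises changed their hours, and the subgroup costings rest on smaller counts still.

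**Working it through.** The document gives no weekly count, standard error, expected effect or cost range, so there is no planned figure to reproduce. Everything below except the exposure shares is illustration under stated assumptions.

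**1. Exposure** (The policy changes section). Glasgow: 10/1350 = 0.7% of on-premises outlets. Aberdeen: 38/430 = 8.8%.

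**2. Width of the hospitalisation scenarios.** Take cost per call-out = A + c(E + hH), where A is the ambulance cost, c the share conveyed, E the A&E cost, H the inpatient cost and h the hospitalised share. The document gives h = 5%, 10%, 15%. Assumed: c = 0.5 to 0.9, E = 0.5A to 1A, H = 3A to 10A. The half-width relative to the 10% case is 0.05cH / (A + cE + 0.10cH).

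- Lowest (c = 0.5, E = A, H = 3A): 0.075/1.65 = 4.5%.
- Highest (c = 0.9, E = 0.5A, H = 10A): 0.45/2.35 = 19.1%.

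**3. Width from sampling error.** With a fixed unit cost, cost is a constant multiple of the effect, so its relative 95% half-width is 1.96/z, with z = estimate/SE. That is 98% at z = 2, 65% at z = 3 and 20% at z = 10. Sampling error falls below the scenario width only when z exceeds 1.96/0.191 = 10 (widest scenarios) to 1.96/0.045 = 43 (narrowest).

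**4. Plausible values of that half-width.** Assumed: weekly weekend-night mean μ = 15 to 120; variance φμ(1+ρ)/(1−ρ) with (φ, ρ) = (1, 0) or (1.5, 0.2); 52 post-policy weeks or all weeks to the end of 2022; a level-change model with or without a linear trend. Pre-policy weeks are about 223 in Glasgow and 200 in Aberdeen, if data start on 1 January 2015 and the Aberdeen break is set at 1 November 2018. Ranges over both cities:

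| True effect | Half-width relative to incremental cost |
|---|---|
| 5% | 35% to 331% |
| 10% | 18% to 166% |
| 16% | 11% to 104% |
| 34% | 5% to 49% |

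The 16% and 34% rows use effect sizes cited in the Introduction, from other settings and outcome windows.

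**5. One case in full.** Aberdeen, μ = 30, 52 post-policy weeks, 10% effect = 3 extra call-outs a week. Take c = 0.75, E = 0.5A, H = 6A.

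- Cost per call-out is 1.60A, 1.825A and 2.05A at h = 5%, 10% and 15%. The scenario range for weekly cost is 3 × 1.60A to 3 × 2.05A, or 4.80A to 6.15A.
- Level-only model, φ = 1, ρ = 0: SE = √[30(1/200 + 1/52)] = 0.85. The effect is 3 ± 1.67 (±56%), and at 1.825A the cost is 2.43A to 8.52A.
- Level plus trend, φ = 1.5, ρ = 0.2: SE = 1.79. The effect is 3 ± 3.51 (±117%), and the cost is −0.93A to 11.88A.

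**6. Subgroups.** Relative error grows as one over the square root of the count. If a deprivation quintile held a fifth of the events and had the same relative effect, its half-width would be √5 = 2.2 times the city figure.

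**The case against.** The strongest defence is that this is a condensed article. The analysis plan it cites is not shown and may give intervals for the effect. Nothing says such intervals will be withheld, and the cost-consequence analysis will report events in natural units beside the costs. With fixed unit costs, anyone holding the effect interval can scale it. That stands as far as it goes: the document does not support a claim that effect uncertainty will go unreported. But this article is the economic evaluation's own protocol and has a section devoted to uncertainty. The costing it describes uses only the point estimate. The alternative controls under Comparators address design uncertainty, not sampling error. Simple scaling also does not give an interval for a total over correlated outcomes.

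Four stronger readings are tempting and should not be drawn:

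- **That a stated cost range is far too narrow.** No range is stated. The comparison depends on counts and effect sizes that are not given, and for a large effect with high counts the ordering can reverse.
- **That the hospitalisation scenarios represent the whole planned range.** They are offered as an example. The crime scenarios have no percentages, and the added perspectives have no stated size, so the full width is unknown.
- **That any published admission figure switches the hospitalisation scenarios off.** The condition is a reliable estimate, and the crime and perspective scenarios carry no such condition.
- **That a city whose effect interval spans zero will be given a wholly positive cost range.** This depends on whether costing is triggered by a demonstrated effect or by any non-zero estimate, and the wording allows either.

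**Conclusion.** The point holds in a limited form. Followed as written, the plan leaves the sampling error of the time-series effect out of every effect-derived cost and out of the cost-effectiveness and cost-analysis results, so the planned ranges understate uncertainty.

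The direction follows from the text; the size does not. Under the assumptions above, the omitted error is in most settings several times the hospitalisation-scenario width for effects of 5% to 10%. For a 34% effect with high weekly counts it is of similar size. Low exposure in both cities makes a small effect plausible, and the subgroup costings are the most exposed. Neither the design nor the effect estimate is affected, but the correction should be in place before the costs are analysed.

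**What to change.** In Analysis of costs and consequences and in Uncertainty and sensitivity analysis, state that for each city, outcome and subgroup:

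- the effect estimate's distribution (by simulation, or a bootstrap that respects autocorrelation) or its 95% limits will be carried through the unit costs, using standard errors that allow for autocorrelation;
- a 95% interval will be reported for each effect-derived cost line and for the cost-effectiveness and cost-analysis results;
- the deterministic scenarios will be kept on top of these intervals, and the hospitalisation-share scenarios will be run even if a literature estimate is adopted.

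The cost is a sentence or two in the protocol and a little extra analysis. Cost results will look less precise. No new data are needed.

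### The crime cost scenarios apply an assumed share of crimes to what reads as an average cost per crime; if it is an average, every such scenario falls on one side of the main estimate

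*Protocol article*

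**What the plan says.** Three places in the protocol article bear on this.

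- **Consequences.** Crime costs are divided into "costs in anticipation of crime, costs as a consequence of crime and costs in response to crime". On valuation it says "The unit cost for the reported crimes will be adopted from published sources", with a publication on the economic and social costs of crime as the example. The same reference supports both statements. No percentage is attached to the unit cost here.
- **Analysis of costs and consequences.** The costing rule is that "the unit cost of each resource will be multiplied by the absolute number of fewer or additional outcomes/consequences". The sentence is introduced by alcohol-related ambulance call-outs, but the article gives no other costing rule for crime.
- **Uncertainty and sensitivity analysis.** The section opens with "We will incorporate deterministic sensitivity analysis to explore multiple scenarios". It gives the hospitalisation example, "if 5%, 10% or 15% of the conveyed alcohol-related ambulance call-outs required hospitalisation", and then carries the same idea over to crime: "we will create cost scenarios for recorded crimes by assuming percentages of recorded crimes incurred anticipation costs", or consequence costs, or response costs. No percentages are given for crime.

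**The concern.** For hospitalisation, an assumed percentage is the right tool. An inpatient stay is a separate event that follows only some conveyed call-outs, and its cost is a cost per admission. The share must be supplied from somewhere.

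A unit cost for reported crimes is ordinarily a different kind of quantity: spending in a cost area divided by the number of crimes. Crimes with no court case or no property loss are already in the denominator and contribute zero. Multiplying that average by an assumed share of crimes that incurred the cost discounts it a second time.

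Two details in the article strengthen the point.

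- The crime counts come from the Police Scotland IT system (Consequences section), so every counted crime has already involved some police activity. Assuming that only a share of them incurred response costs fits poorly with that source, at least for the police part.
- The anticipation examples are burglar alarms and CCTV. That money is spent ahead of crime and is not triggered by an individual offence, so a share of crimes that incurred it has no clear meaning.

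At stake is how informative the crime scenarios are. The section describes deterministic scenarios and no probabilistic analysis, so these scenarios are the stated way of showing uncertainty in the crime cost. A range that can only move towards zero does not do that.

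**Working it through.** The article states no crime unit cost and no crime percentage, so there is no figure of the plan's own to reproduce. The check is algebraic.

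**Notation**

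- dN: estimated change in reported crimes (from the time series analysis)
- c: cost in one area for a crime that incurs it
- p: true share of crimes that incur it
- q: share assumed in a scenario

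The correct component cost is dN × p × c.

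**Case A: the published unit cost is an average over all crimes, that is p × c.**
Full application gives dN × (p × c), which is correct. The scenario gives dN × q × (p × c). Scenario divided by correct = q, whatever p is.

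**Case B: the published unit cost is per crime that incurs the cost, that is c.**
The scenario gives dN × q × c. Scenario divided by correct = q/p. A share is needed here, and the result may be too low, exact or too high.

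**Illustration with assumed values:** dN = 100, c = £1,000, p = 0.50. The correct cost is 100 × 0.50 × £1,000 = £50,000, and the all-crime average is 0.50 × £1,000 = £500.

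| Assumed q | Case A: 100 × q × £500 | Ratio | Case B: 100 × q × £1,000 | Ratio |
|---|---|---|---|---|
| 0.25 | £12,500 | 0.25 | £25,000 | 0.50 |
| 0.50 | £25,000 | 0.50 | £50,000 | 1.00 |
| 0.75 | £37,500 | 0.75 | £75,000 | 1.50 |
| 1.00 | £50,000 | 1.00 | £100,000 | 2.00 |

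In case A the shortfall is 1 − q: 75%, 50%, 25% and 0%. No choice of q up to 100% gives a value above the one the unit cost implies. In case B the scenarios fall on both sides of the correct value.

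**All three areas together (case A).** The ratio for the total is the average of the three shares, weighted by each area's part of the unit cost. It cannot exceed 1. With three areas of equal size (an assumption) and q = 0.50 in each, it is (0.50 + 0.50 + 0.50)/3 = 0.50.

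**Direction.** The costing rule allows for fewer or more outcomes. If dN is positive, an added cost shrinks. If dN is negative, a saving shrinks. Either way the change moves towards zero.

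**The case against.** The strongest reply is that the error is conditional on things the article does not state. It never says that a percentage multiplies the published unit cost; that follows from the analogy with hospitalisation and from the general costing rule. Whether the figure is an all-crime average or conditional on the cost being incurred depends on a cited source that is not at hand, and that source is named only as an example. With conditional figures the percentage method is legitimate. All of this stands, and the point is therefore worded as conditional.

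A second reply is that a share below 100% may be deliberate. An additional weekend-night offence need not cause anyone to buy an alarm, and the criminal justice costs listed in the overview of the economic analysis (police, justice system, physical and emotional harm) do not mention anticipation. This is a fair reason to leave anticipation costs out of a scenario. It supports excluding the area openly, not assigning it a partial share of crimes.

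Three stronger readings might be inferred, and the documents do not support them.

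- **That the main crime cost is understated.** The percentages appear only under Uncertainty and sensitivity analysis. The unit cost in the Consequences section carries none.
- **That harm from later hours will look smaller.** This holds only if crimes rise; if they fall, the saving looks smaller.
- **That the understatement is about 6.7-fold to 20-fold.** That comes from 1/0.15 and 1/0.05, with values the article gives only for hospitalisation of conveyed call-outs. It gives none for crime.

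**Conclusion.** The point holds for the scenario analyses, on two assumptions: that the adopted crime unit cost is averaged over all crimes, which is the ordinary reading of the article's wording, and that the assumed share is applied to it, which is what the parallel with hospitalisation implies. Each scenario component is then q times the value implied by the unit cost. Every scenario with q below 100% lies on the same side of the main estimate, closer to zero, and the resulting range does not describe uncertainty in crime cost. The size cannot be fixed from the document; for illustrative shares of 75%, 50% and 25% the components are 25%, 50% and 75% too small.

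The main crime estimate, unit cost times the change in crimes, is not shown to be affected. If the adopted figures are conditional on the cost being incurred, the percentage is valid and the point falls away for those components. The article leaves this open, and the choice of scenario method depends on it.

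**What to change.** Amend the crime sentence under Uncertainty and sensitivity analysis along these lines:

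1. State, for each adopted crime cost component, whether the source averages it over all crimes or reports it per triggering event.
2. Where it is averaged over all crimes, apply it in full to the estimated change in crimes. Build scenarios by including or excluding whole cost areas (for example, with and without anticipation costs) and by varying the unit costs over published low and high values or a stated plus/minus percentage. Varying the unit cost lets the range extend to both sides of the main estimate. Excluding an area still lowers the total, but as a visible choice about scope.
3. Use an assumed percentage of crimes only for costs the source reports per triggering event, for example per prosecution, and say so.

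The cost is a few sentences, no new data, and slightly more reporting because results are shown by cost area. The scenario crime costs, or savings, will be larger than under the percentage approach.
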